### Randomization and treatment allocation

The randomization of the three branches of the study will be carried out on a centralized basis, by a statistician who is otherwise unrelated to the study, using a 1:1:1 scheme in blocks of 12 and stratifying by clinics. There will be the same number of sets of envelopes as there are of participating midwives/clinics (some 40 midwives are expected to take part). Each set will contain 12 opaque envelopes which will be sealed after the introduction of a card with the letter corresponding to the allocation to the group as determined by the software-generated sequence: Group A (true moxibustion), Group B (sham moxibustion) and Group C (control). After the baseline assessment and the signing of informed consent, these sealed, opaque, numbered envelopes will be used in sequence to assign the study subjects to one of the three groups. The collaborating midwife will note on the card the pregnant woman number and that of the clinic. At the end of the study, the chief researcher will check each card against the original randomization list to confirm that all the subjects received the treatment that had been assigned to them. This method ensures that neither the clinics nor the healthcare professionals taking part in the study will be involved in the randomization process and thus will not be able to influence it. A patient may be withdrawn from the study at any time, at her discretion or that of the researcher. The reasons for this will be noted down on the summary page of the Data Collection Record (DCR). The midwives who participate in the study have attended a 10-hour training course on postural recommendations and moxibustion techniques, and in which criteria for data collection were standardised.

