## Discussion

As observed above, the problem identified by the analysts of the only Cochrane review available is the low methodological quality of most of the studies that have been made. In designing the present study, special care was taken regarding the characteristics conforming a quality RCT, in accordance with the recommendations made by Jadad [18]. Nevertheless, the following foreseeable limitations should be pointed out: firstly, the sample was extracted from the universe of pregnancies managed within the Andalusian Public Healthcare System (SSPA), and therefore the conclusions drawn will only be applicable to this population group. The complexity of including private clinics in the study led us to renounce this idea, especially in view of the fact that the coverage of the pregnancy control programme within the public system is almost universal; moreover, the pregnant women who make use of private systems do not stop receiving the follow-up attention scheduled under the public healthcare system. From the bibliographic review performed, neither does it seem that social class influences the incidence of breech presentation or its version during gestation. It is very likely, therefore, that the results obtained will resemble those that would be derived for the entire population of pregnant women in Andalusia. The inclusion of a routine control of the official programme (an echography performed in week 32) also avoids possible selection bias. Thus, with the involvement of the gynaecologist performing this examination, and of the midwife who participates in routine care, the uptake is ensured of 100% of the cases of NCP detected during the study period, while the rate of losses to follow up is minimised.

Secondly, there exists the possibility (which has actually occurred in other studies) of a pregnant woman refusing to take part when she discovers which branch of the research study she has been assigned to. This is applicable to the formation of the control group, as normally any intervention (whether true or sham moxibustion) will be willingly accepted by a pregnant woman in a situation of some risk. In the studies examined, this has actually occurred in only a very small percentage of cases, but note should be taken of this possible source of bias.

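### The only described link between a woman and her envelope is made after the allocation is visible, so the claim that staff cannot influence allocation is not supported for the use of the sequence

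*Protocol article*

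**What the plan says.** All the steps are in the Protocol article, Methods, Randomization and treatment allocation.

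- Preparation: "Each set will contain 12 opaque envelopes which will be sealed after the introduction of a card with the letter corresponding to the allocation".
- Use: "After the baseline assessment and the signing of informed consent, these sealed, opaque, numbered envelopes will be used in sequence".
- Recording: "The collaborating midwife will note on the card the pregnant woman number and that of the clinic".
- Final check: "the chief researcher will check each card against the original randomization list to confirm that all the subjects received the treatment".
- Assurance: the section concludes that neither the clinics nor the staff "will be involved in the randomization process and thus will not be able to influence it".

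The Discussion foresees that a woman may decline once she learns her group. It ties this to the control group, because "normally any intervention (whether true or sham moxibustion) will be willingly accepted by a pregnant woman in a situation of some risk". It adds that in earlier studies this happened in only a very small share of cases, and it names it as a possible source of bias.

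**The concern.** Sealed envelopes protect a trial at two stages. The sequence must be unpredictable, and each envelope must be tied to one woman before anyone sees what is in it. The article deals fully with the first stage through central generation by an outside statistician. For the second it describes one record, and that record is made on the object that carries the allocation.

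If an opened envelope is used for someone else, or kept for the next woman after a refusal, the groups are no longer formed by chance alone. The comparison at stake is moxibustion against usual care, on which the sample size and the primary logistic model both rest. A refusal that leaves no trace on the card also removes a randomised woman from the intention-to-treat count. Neither event needs bad faith. The weakness does not depend on block length, and the missing link cannot be reconstructed after enrolment.

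**Working it through.** **Reading the steps together**

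1. The card goes into the envelope before sealing, so the letter and the space for the woman's number are on the same card, inside.
2. The envelope is used after baseline assessment and consent. The woman's number can be written on the card only once the envelope is open. The article does not state this order in words; it follows from the physical arrangement.
3. The final check compares card with list. The card was made from the list, so its letter agrees whoever's number is written on it:

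| What happened | Card letter against list | What would reveal it |
|---|---|---|
| Next envelope used for the next woman | agrees | nothing to reveal |
| Opened envelope used for another woman | agrees | woman numbers fixed beforehand and out of step with envelope order |
| Woman declines before her number is written, card reused for the next woman | agrees | a gap in woman numbers fixed beforehand |

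4. The last column needs a number issued independently of the envelope and a comparison of the two orders. The article describes neither, and it does not say when the number is issued.
5. Central generation stops staff from shaping the list. It does not govern what happens when about 40 midwives open envelopes.

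**Illustration of size**

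The plan gives no figure on this point. Its total of 492 supplies the denominators. That total reproduces closely: 50% against 70%, two-sided 0.05 and 90% power need 124 per arm; 124/0.75 rounds up to 166; 3 × 166 = 498, which is 1.2% above 492.

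Inputs from the plan: 492/3 = 164 control women and 328 in the two moxibustion groups together. Inputs assumed, with no source in the document: 5% or 10% of all women exchanged; a 20-point gap in the chance of turning (60% against 40%); the more favourable woman always going to moxibustion.

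Each exchanged pair lowers the control total by the gap and raises the moxibustion total by the gap:

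bias = pairs × gap × (1/164 + 1/328)

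- 5%: 0.05 × 492/2 = 12.3 pairs; 12.3 × 0.20 × 0.00915 = 0.0225, about 2.3 points.
- 10%: 0.10 × 492/2 = 24.6 pairs; 24.6 × 0.20 × 0.00915 = 0.045, or 4.5 points.

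Reuse after refusal has a smaller effect, because only the control group changes. If a share r of women who draw control decline and are replaced, and they differ by g from those who accept, the control rate shifts by r × g. With r at the same assumed 5% to 10% and g = 0.20, that is 0.05 × 0.20 = 1 point to 0.10 × 0.20 = 2 points.

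**The case against.** The article lists the recognised safeguards: an outside statistician, a software-generated list, opaque sealed numbered envelopes, use in order, opening only after consent, and a final reconciliation. What is written on the outside of the envelope, and whether a dated enrolment log exists, is detail that a condensed article may leave to the full protocol. The assurance can be read as covering generation only, where it is true. The final check is presented as confirming treatment received, not as a test for exchanges.

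Much of this stands. A reader might infer that the woman's number first comes into being on the card, or that the final check could never detect an exchange. The text supports neither. The number may be issued at consent, and an audit that compared number order with envelope order would then show a departure. A reader might also infer that the Discussion foresees midwives exchanging envelopes. It speaks of women declining, and rarely.

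Exchanging two women would also be hard to arrange. With 492/40 = 12.3 women per midwife over the 33 months from April 2008 to December 2010, and even recruitment, a midwife enrols one woman about every 33/12.3 = 2.7 months. The 10% case would need 24.6/164 = 15% of control places to be exchanged. Reuse after a refusal needs no second woman at hand, so this argument does not remove it.

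The objection does not remove the point itself. The article sets out a specific recording step and a specific check, and then says that the method ensures staff cannot influence the process. The step described is weaker than an equally simple one, and the conclusion goes further than the steps do.

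**Conclusion.** The point holds as a cheap improvement to a stated step, and as a correction to an assurance worded too strongly. It rests on two things in the text: the card is inside the sealed envelope, and no earlier link or order comparison is described. If the full protocol fixes the woman's number before opening and checks its order against the envelopes, only the wording of the assurance needs attention.

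Nothing in the article shows that exchanges would occur, or how often. The 2.3 to 4.5 points depend wholly on the assumed exchange rate, gap and direction. Willingness to accept an arm is not prognosis, so even the direction is not given. A reader might carry the upper figure forward to an inflated false-positive rate; the document gives no basis for that, and I do not rest the point on it.

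**What to change.** In Randomization and treatment allocation:

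1. Have the midwife write the woman's number, the date and her initials on the outside of the next numbered envelope before opening it, and keep the envelope with the card.
2. Extend the end-of-study check to compare envelope order with consent and opening dates within each clinic, in addition to comparing letters with the list.
3. Limit the assurance to generation of the sequence, or restate it for the procedure as amended.

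The cost is one line in the midwives' instructions, a little more recording at each enrolment and a slightly longer final check. Sample size, allocation ratio and analysis are unchanged. It has to be in place before the first envelope is opened.

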### Sample size

The sample size has been predetermined at n = 492 patients, for a significance level of 95%, a power of 90% and a difference in the success rates of either of the intervention groups (A or B) with the control group (C) of 20%, assuming a dropout rate of 25%. These values were calculated using SamplePower version 2 software.

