Acupuncture and moxibustion are therapeutic techniques found in traditional Chinese medicine. They have been employed since ancient times, and specific recommendations in Chinese texts include the application of heat (moxibustion) by the combustion of *Artemisia vulgaris *(moxa) over an acupuncture point in order to correct NCP [12,13]. This latter point, known as *Zhiyin *(BL67) is located in the outer corner of the little toenail. In addition to moxibustion, acupuncture may also be used, either alone or in association with moxibustion, on this or other points, although it has been found that the highest level of effectiveness is associated with the application of moxibustion alone [14]. A Cochrane review [15] concluded that there is insufficient evidence from the studies included in its analysis, and observed that there have been few well-designed studies (only 3 are included in the review) and that most of them used a small sample. Some studies with a larger sample, such as that by Kanakura et al. [16], were not randomized. A larger, systematic review that we have carried out this year (manuscript submitted for publication), with the inclusion of new studies performed to date, and with the incorporation of those published in Chinese in the last 10 years, shows that studies contain to be of low methodological quality. We estimate a correction rate of 70% (versus 50% in control groups) among pregnant women treated with moxibustion. Among the studies carried out so far, no reports have been made of side effects, although the smoke generated while the moxa is burned may irritate the respiratory tracts. Nevertheless, there is no evidence to support this hypothesis [15]. Neri et al. [14,17] have made a cardiotocographic study of the effects of moxibustion on foetal heartbeat, and concluded that no harm is caused by this process.

The present study is funded by the Health Ministry of the Andalusian Regional Government (Project No. 0053/2007).

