For the primary outcome variable, logistic regression models will be created, using ITT analysis. These will include, firstly, the group variables (experimental vs control), taking the control group (usual care) as the reference level. Then, the model will be adjusted for the variables of age, parity and weeks of gestation at randomization (the baseline variables). Adjustment will also be made for other possible confounders (the variables that are imbalanced in the baseline analysis) using criteria of statistical significance (*P *< 0.05) and of confusion (change of over 10% according to the magnitude estimator – the incidence odds ratio). The detection of possible interactions with the "treatment group" variable will be carried out by means of statistical significance criteria for the corresponding terms of interaction, introducing the relevant additive and multiplicative interaction variables. The level of significance will be set at <0.05 α for the global comparisons, although this level will be penalized by the existence of an intermediate level, as explained below. A cost effectiveness analysis, from the standpoint of the Andalusian Public Healthcare System, will be performed.

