#### Intermediate analysis

An intermediate analysis will be performed when the follow up of half of the total sample has concluded and the results of this are known, using multiple Bonferroni tests, and establishing a level of statistical significance for 2 tests at *P *< 0.025. This penalization is necessary to avoid exaggeration of any type I error.

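### The sample size claims 90% power at the 0.05 level, but the plan tests at P < 0.025 at both looks; power per comparison is then about 85% on the most plausible planning rates

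*Protocol article*

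**What the plan says.** Three sections of the protocol article bear on this.

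- **Sample size:** "The sample size has been predetermined at n = 492 patients, for a significance level of 95%, a power of 90" per cent. The effect is "a difference in the success rates of either of the intervention groups (A or B) with the control group (C) of 20" per cent, "assuming a dropout rate of 25" per cent. No control-arm rate is given, and no adjustment for an interim look is mentioned.
- **Statistical analysis:** significance is set at 0.05 for the global comparisons, but "although this level will be penalized by the existence of an intermediate level, as explained below".
- **Intermediate analysis:** one interim is planned once half of the sample has completed follow-up, "using multiple Bonferroni tests, and establishing a level of statistical significance for 2 tests at" P < 0.025.

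Two further inputs come from elsewhere in the article. The Background says: "We estimate a correction rate of 70% (versus 50% in control groups) among pregnant women treated with moxibustion". The Randomization section specifies allocation "using a 1:1:1 scheme in blocks of 12 and stratifying by clinics".

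**The concern.** The sample size uses one significance level and the tests use another. If 492 is the number needed for 90% power at 0.05, the same number must give less than 90% when the final test is held to 0.025. The early chance to reject at the interim recovers only a little of the loss.

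What is at stake is how a null result would be read. The article faults earlier trials for small samples and presents this one as powered at 90%. If the design as tested has about 85%, the chance of missing the planned effect on the primary outcome is about 15%, not 10%.

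**Working it through.** **Inputs**

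- N = 492, allocated 1:1:1: 492 / 3 = 164 per arm.
- Dropout 25%: 164 × 0.75 = 123 evaluable per arm.
- Difference 20 points, each intervention arm against control.
- Significance level of 95%, read as two-sided 0.05.
- Rates 70% against 50%. This is an assumption taken from the Background.
- Two looks, at half and full information, each at two-sided 0.025.

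**Step 1: reproduce the plan's figure**

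The pooled two-proportion formula, without continuity correction, is

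n = [z(1−α/2)·√(2·p̄(1−p̄)) + z(0.90)·√(p1(1−p1) + p2(1−p2))]² / d²

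with p̄ = 0.60, √0.48 = 0.6928, √(0.25 + 0.21) = 0.6782 and d = 0.20.

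At α = 0.05: n = (1.960 × 0.6928 + 1.2816 × 0.6782)² / 0.04 = 124.0, so 124 per arm. Then 124 / 0.75 = 165.3, rounded up to 166, and 166 × 3 = 498. The unpooled formula gives 486 and the arcsine formula 501, so 492 lies within the range for an unadjusted two-sided 0.05. A one-sided 0.05 needs only 101 per arm, or 405 in total (101 / 0.75, rounded up to 135, × 3), and does not reproduce it.

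Two other routes also come close. One is 40% against 60% with dropout applied as × 1.25 (489). The other is 70% against 50% with continuity correction and × 1.25 (504). Both also use 0.05.

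**Step 2: power of the stated sample at each level**

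Power = Φ{[d√n − z(1−α/2)·0.6928] / 0.6782}, with n = 123 and d√n = 2.218.

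- α = 0.05: (2.218 − 1.358) / 0.6782 = 1.268, power 89.8%.
- α = 0.025: (2.218 − 1.553) / 0.6782 = 0.981, power 83.7%.

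The unpooled formula gives 84.8% at 0.025.

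**Step 3: count both looks**

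The rule allows rejection at either look. Simulating 1,000,000 trials with looks at 61 and 123 per arm, both at 0.025, gives power of about 51% at the interim and 84.9% over both looks. Normal-theory calculations give 84.7% to 86.2%, depending on the variance formula. Type I error per comparison over both looks is about 4.2% by simulation and 4.3% by normal theory.

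**Step 4: vary the unstated rates (123 evaluable per arm)**

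| Control vs treated | 0.05, single test | 0.025, final look | 0.025, both looks |
|---|---|---|---|
| 40% vs 60% | 88.5% | 82.0% | about 84% |
| 50% vs 70% | 89.8% | 83.7% | about 85% |
| 60% vs 80% | 93.3% | 88.7% | about 90% |

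**Step 5: vary dropout (50% vs 70%, both looks at 0.025)**

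Power is about 87–88% at 20% dropout, about 90% at 13% and about 94% with none.

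**Step 6: sample needed to keep both 90% and the 0.025 rule**

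Counting the final test alone: (2.241 × 0.6928 + 1.2816 × 0.6782)² / 0.04 = 146.7, so 147 per arm. Then 147 / 0.75 = 196, and 196 × 3 = 588. Counting both looks: about 142 per arm. Then 142 / 0.75 = 189.3, rounded up to 190, and 190 × 3 = 570.

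**The case against.** **The rates are not stated.** The Sample size section gives only a difference, and the Background does not link its 70% and 50% to the calculation. This stands, and the size of the loss depends on it. At 60% against 80%, two-look power is about 90%, and a reader might infer that the interim had been allowed for. The text does not support that: it names a 95% level, and at 0.05 those rates would need only 438 women. The mismatch between sections holds for any control rate.

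**Dropout may be lower.** The Discussion says that losses will be minimised, and the intention-to-treat analysis keeps every woman with valid data. If dropout is about 13%, power is back to 90%. This also stands, so the shortfall is not a fixed property of the trial. But the 90% is itself claimed under 25% dropout, so it should be judged there.

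**The two tests may be the two arm comparisons.** The Statistical analysis section ties the reduction to the intermediate analysis, and the threshold appears under that heading, so two looks is the natural reading. On the other reading the trial is still sized at 0.05 and tested at 0.025.

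**Stronger readings to avoid.** A reader might infer that the equal Bonferroni split is itself a mistake. It is valid and slightly conservative; preferring another boundary is a design choice. A reader might quote a miss risk of 16%, but that counts the final look alone; the rule as written gives about 15%. Nor do the documents show that 588 women are needed: that figure ignores the interim, and it matters only if 90% and 0.025 are both to be kept.

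**Conclusion.** The point holds as an inconsistency between sections. The sample size and its 90% power rest on an unadjusted two-sided 0.05, while the plan tests at 0.025 at both the interim and the final analysis. The sample size arithmetic is right for the level it names.

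With 123 evaluable per arm and 70% against 50%, power per comparison falls from about 90% to about 85% over both looks (about 84% at the final look alone). This assumes the Background rates and the full 25% dropout. Across control rates of 40% to 60%, two-look power runs from about 84% to about 90%.

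This should be fixed, but it does not invalidate the trial. Type I error per comparison stays below 5%, no estimate is biased, and about 85% is still a conventional level of power. What needs correcting is a stated figure.

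**What to change.** Bring the Sample size section into line with the Intermediate analysis section. State the assumed control rate, say that each look is tested at P < 0.025, and give the power as about 85% per comparison for 492 women with 25% dropout (if 50% is confirmed as the control rate). This costs a few sentences and changes neither the recruitment target nor the testing rule.

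As an option, the sponsor could pre-specify an O'Brien-Fleming-type boundary instead, at about P < 0.005 for the interim and P < 0.048 for the final test. On the same assumptions this gives about 89% power with a type I error of about 5.0% per comparison, again without more women. It has two costs:

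- The chance of crossing at the interim under the planned effect falls from about 51% to about 29%.
- Familywise error across the two comparisons with the shared control rises from about 8% to about 9% by simulation, unless it is controlled separately.

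If 90% power and the 0.025 rule are both to be kept, the target becomes about 570 women counting both looks, or 588 counting the final test alone.
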